# 2. PROTOCOL SYNOPSIS

**Study Title:** Pregabalin for chronic cough in patients with lung cancer: a randomized double-blind placebo-controlled trial.

**Aim**: To evaluate the efficacy and safety of pregabalin in improving the severity of cough in patients with lung cancer compared to placebo.

**Primary Objective:** To study the effect of pregabalin (maximal tolerated dose of 300 mg per day) as compared to placebo on cough severity as measured by the Visual Analog Scale (VAS) between baseline and 9 weeks of treatment.

**Secondary Objectives:**

- To study the effect of pregabalin (maximal tolerated dose of 300 mg per day) as compared to placebo on cough severity as measured by the Manchester Cough in Lung Cancer Scale (MCLCS) score between baseline and 9 weeks of treatment.
- To study the change in VAS and MCLCS scores between baseline and day 7 of therapy with pregabalin (maximal tolerable dose of 300 mg per day) as compared to matching placebo.
- To study the effect of pregabalin therapy as compared to placebo on improvement in quality of life (QoL) in lung cancer patients with chronic cough.
- To describe the adverse effects of pregabalin in lung cancer patients with chronic cough.

**Study Population**

Patients with suspected/diagnosed advanced lung cancer presenting with cough lasting for 2 or more weeks and planned for palliative intent therapy.

**Sample Size:** 166

**Treatment Plan:**

Patients with advanced lung cancer complaining of cough lasting for 2 or more weeks will be randomized to receive either pregabalin (at maximal tolerated dose of 300 mg orally daily) (Arm A) or a placebo (Arm B).

Severity of cough will be assessed using Visual Analog Scale (VAS) and Manchester Cough in Lung Cancer Scale (MCLCS). QoL will be assessed using the EORTC QLQ C30 and LC13. VAS, MCLCS and QoL forms will be administered at the time of enrolment in the study, on day 7, and at the end of study visit (9 weeks). Toxicity data will be collected at every visit.

**Duration of Study:** 24 Months

# 1. INTRODUCTION

Cough is a distressing symptom afflicting nearly 90% of patients with lung cancer(1). Adequate cough suppression in lung cancer patients is an unmet clinical need and requires strategies beyond current medical practice. Development of effective antitussives is hampered by our lack of understanding of complex cough pathways and objective tools for assessment of cough severity. Advances in cancer management have led to improved survival of patients with incurable lung cancer thereby making palliation of chronic cough necessary in clinical care.(2)

Although the epidemiological definition of chronic cough is cough that has lasted for three or more months, the current clinical guidelines use an arbitrary cut-off of eight weeks (3). This definition of chronic cough is applicable for non-malignant causes of cough. In patients with cough due to lung cancer, there is a need for a revised definition, given the patient’s limited life expectancy. Since cough lasting for two or more weeks requires radiological and laboratory evaluation for an underlying pathological condition namely, tuberculosis and lung cancer, we have decided to adopt this as our definition for chronic cough in lung cancer for the purpose of this study. We find this a clinically relevant definition which facilitates timely evaluation and diagnosis.

Although only 2% of these patients are likely to have lung cancer, nearly 65% of patients with cancer have cough at presentation (4). Understanding the central and peripheral mechanisms of cough in lung cancer is imperative to finding effective antitussive strategies. The cough reflex is fundamentally a defensive mechanism. Peripheral pathways comprise of Aδ fibers carrying fast conducting stimuli from larger airways and C fibers from small airways which relay slow conducting, inhibitory cough signal via the vagus nerve. These communicate with central cough pathways via two neurotransmitters, neurokinin A and glutamate. (5) Albeit the central efferent cough center is located in the medulla oblongata, it is subject to modulation by supramedullary and pain pathways.

Chronic cough can be considered akin to neuropathic pain. It is likely that opiates and neuromodulatory drugs like gabapentin and pregabalin exert an antitussive effect by influencing pain pathways (6). Cough in lung cancer can be related to a large central tumor stimulating Aδ fibers or interstitial lesions damaging the inhibitory C fibers (5).

The three domains of cough severity are its intensity, frequency and disruptiveness. When evaluating any drug for efficacy against cough, it is important to use validated tools to assess cough severity and the impact of cough on quality of life (QoL), so that the efficacy of various drugs or interventions can be compared between studies. The Visual Analog Scale (VAS) is a simple and reproducible subjective tool to assess cough severity. The VAS is a 10 cm line, marked 0 at one end and 100 mm at the other end. The end marked 0 is labelled as ‘No cough’ and the end labelled as 100 mm is marked ‘worst cough ever’. The patient is asked to mark the point on the line that best correlates with his/her cough in terms of his/her perceived severity. A higher score indicates worse cough severity. VAS has been described and validated in patients with lung cancer (16,17). A seven-item Cough Severity Diary is another subjective tool evaluating all three domains of cough [disruptive (two items), frequency (three items) and intensity (two items)] (7). Objective evaluation of cough frequency can be performed by ambulatory cough monitoring (ACM). This involves the patient strapping on a recording device with a miniature microphone for up to 24 hours. Its interpretation is complex and remains unvalidated in patients with cough related to lung cancer. Manchester Cough in Lung Cancer Scale (MCLCS) was one of the earliest tools to be extensively studied in lung cancer patients. It assesses the severity, frequency, distress and the impact of cough. MCLCS is a questionnaire consisting of ten questions that describe the patient’s cough experience in the preceding week; each question has five possible answers scored as one (never) to five (all the time); the score ranges from one to fifty; higher score indicates worse cough impact. In addition, The Leicester cough questionnaire (LCQ) and the cough-specific quality of life questionnaire (CQLQ) are also useful health status questionnaires for adults with chronic cough. EORTC Q30 and the lung cancer specific LC13 questionnaire have been used to evaluate global QoL in lung cancer patients. However, a validated tool evaluating cough specific QoL in lung cancer patients is lacking (8).

Neuromodulatory drugs like gabapentin and pregabalin have been successfully tried in neuropathic pain. Their utility in cough suppression too has been studied in small randomized trials though none of the trials involved patients with lung cancer. A study in 2012 compared gabapentin to placebo for chronic cough. 32 patients randomized to the gabapentin arm were found to have improved cough specific QoL (difference in LCQ score of 1.8; P=0.004) (12). At the dose used (maximum dose of 1800 mg/day), 30% of the patients treated with gabapentin had significant side-effects notably fatigue and nausea, as compared to 10% of patients in the placebo arm. Pregabalin 300 mg daily in addition to speech pathology therapy (SPT) was also studied in a similar population of patients suffering from chronic cough (13). In a randomized trial in 40 patients, suppression of cough was found to be better with the addition of pregabalin to SPT as compared to a placebo; the difference in the LCQ score was 3.50; 95% CI, 1.1-5.8; P=0.024 (13). Although the two drugs, pregabalin and gabapentin, have not directly been compared, it seems that at effective doses pregabalin may have resulted in better improvement in cough related QoL (13). An interesting point to note is that the positive effects of pregabalin continued well after stopping the drug though the same was not observed for gabapentin (12,13).

Despite the use of adequate antitussive medications and appropriate doses of opioids, cough remains ‘very distressing’ in 22% patients (14). Given the lacunae in evidence-based management of cough there is a need for newer effective antitussive treatments in lung cancer patients. We propose a study evaluating the role of pregabalin as an antitussive therapy in treating chronic cough in patients with lung cancer.

# AIMS and OBJECTIVES

## Study Hypothesis

The use of the neuromodulatory drug, pregabalin, will reduce cough severity in patients with lung cancer.

## Aim

## To evaluate the efficacy and safety of pregabalin in decreasing the severity of cough in patients with lung cancer compared to placebo.

# Objective

### Primary objective

To study the change in Visual Analog Scale (VAS) scores between baseline and week 9 of treatment with pregabalin (at maximal tolerated dose of 300 mg per day) as compared to placebo.

### Secondary objectives

1. To study the change in Manchester Cough in Lung Cancer Scale (MCLCS) scores between baseline and week 9 of treatment with pregabalin (at maximal tolerated dose of 300 mg per day) as compared to placebo.
2. To study the change in VAS and MCLCS scores between baseline and day 7 of treatment with pregabalin (at maximal tolerated dose of 300 mg per day) compared to placebo.
3. To study the effect of pregabalin (at maximal tolerated dose of 300 mg per day) versus placebo on improvement in quality of life (QOL) in lung cancer patients with chronic cough using EORTC QOL questionnaires.
4. To describe the adverse effects of pregabalin in lung cancer patients with chronic cough.

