### **3.5 Dose escalation schedule:**

Pregabalin or placebo will be started from the day of randomization and the dose will be escalated provided the patient is not experiencing excess toxicity as per the dose escalation schedule described in the table given below. Once dose escalation is completed, pregabalin 300 mg or placebo orally daily will be continued until 9 weeks, i.e. until the first restaging imaging study is performed. After efficacy assessment is completed, pregabalin or the placebo will be tapered (again according to the protocol) over 6 days and then discontinued.

| **Phase** | **Days** | **Daily dose (mg)** | **Schedule (1 capsule=75 mg)** |
| --- | --- | --- | --- |
| Escalation | 1-2 | 75 | 1 capsule, morning |
|  | 3-4 | 150 | 1 capsule, morning and evening |
|  | 5-6 | 225 | 1 capsule, morning, midday and evening |
| Maximal treatment | 7 days to 9 weeks | 300 | 1 capsule, morning and midday;  2 capsules, evening |
| Reduction (start after week 9, once efficacy has been assessed); day numbers counted from the date of assessment of efficacy. | 1-2 | 225 | 1 capsule, morning, midday and evening |
|  | 3-4 | 150 | 1 capsule, morning and evening |
|  | 5-6 | 75 | 1 capsule, morning |
|  | 7 | 0 | Stop |

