### 3.6 **Study procedures**

Persons being evaluated for lung cancer in the thoracic medical oncology outpatient department at Tata Memorial Hospital will be questioned about the presence and severity of cough. Patients with cough will be assessed for eligibility. If found eligible and willing to participate in the trial, written informed consent will be obtained. The patient will then be randomized by computer generated blocks to either Arm A (pregabalin 300 mg orally daily) or Arm B (placebo). Investigators, research staff and the patients will be blinded to the study arm. Baseline laboratory tests performed within a week from the date of randomization to assess organ function i.e., complete hemogram, liver and renal function tests and serum electrolytes (sodium, potassium, magnesium, calcium) will be accepted. Evaluation of the performance status and physical examination will be performed by the treating physician. Pulse and blood pressure will be recorded at baseline and every visit.

Information regarding medications that the patient is taking, including additional antitussive medications will be recorded. Plan for oncologic therapy will also be noted.

Tools for assessing cough severity (VAS, MCLCS) will be administered at baseline, on day 7 (+/- 3 days) and 9 weeks (+/- 7 days) from randomization. In patients who are unable to fill out the questionnaires on their own or have trouble reading, the research staff or social workers will help them.

QoL will be assessed using EORCTC QLQ-Q30 and LC13 questionnaires for lung cancer at baseline, day 7 (+/- 3 days) and 9 weeks (+/- 7 days). In patients who are unable to fill out the questionnaires on their own or have trouble reading, the research staff or social workers will help them.

Toxicity data will be recorded and treated as appropriate. The side-effects will be graded according to the Common Terminology Criteria for Adverse Events (CTCAE) v.5. Detailed description of anticipated toxicity and frequency from pregabalin is provided in the next section on adverse events.

- 1. **Adverse events of pregabalin**: In the phase II study evaluating the role of pregabalin and speech pathology combination therapy for patients with chronic refractory cough, the most frequently noted side-effects (all grades) that occurred more commonly with pregabalin as compared to placebo included dizziness (45%), weight gain (25%), blurred vision (20%) and cognitive changes (30%) (13).

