To measure cough severity, the VAS score at 9 weeks will be subtracted from the baseline score. The means of the change from the baseline scores will be calculated for all patients in each arm and the means will be compared between the two arms using two-sided Student’s t-test. A *P* value of <0.05 will be considered significant. The effect size will be determined with the use of Cohen’s d statistic, which is a measure of the difference between two means divided by an estimate of a pooled standard deviation. As per conventional classification, an effect size of 0.2 will be considered small, 0.5 moderate, and 0.8 large (19). A similar methodology will be used to evaluate the cough impact using the MCLCS. The change in the VAS scores and MCLCS scores from baseline to day 7 to 9 weeks and will be explored graphically between the arms.

QoL data will be scored as per the procedure described in the EORTC scoring manual (15,16). Different subdomain wise QoL data will be generated from the QoL dataset. A subdomain wise comparison was performed between the arms, using the linear mixed effect model.

The difference in toxicities between the two arms will be compared using the Pearson chi-square test or Fisher Exact test.

**6. Feasibility of the Study:** We see approximately 1300 lung cancer patients in a year at Tata Memorial Hospital. We expect to complete the study within 24 months of approval of study.

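### The day-7 objective carries a 300 mg label, but its visit falls during or just after dose escalation and the protocol offers only a graph for the comparison

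*Protocol*

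**What the plan says.** - **Secondary objectives.** Objective 2 is the change in VAS and MCLCS "between baseline and day 7 of treatment with pregabalin (at maximal tolerated dose of 300 mg per day", set against placebo. The synopsis attaches the same dose label: "between baseline and day 7 of therapy with pregabalin (maximal tolerable dose of 300 mg per day".
- **Section 3.5.** Dosing begins on the day of randomisation. The table schedules 75 mg on days 1-2, 150 mg on days 3-4 and 225 mg on days 5-6; the 300 mg row covers "7 days to 9 weeks". Section 3.4, by contrast, describes an escalation of 7 days.
- **Section 3.6.** The cough tools "will be administered at baseline, on day 7 (+/- 3 days) and 9 weeks (+/- 7 days) from randomization".
- **Introduction.** MCLCS asks about "cough experience in the preceding week". No recall period is given for the VAS.
- **Section 5.2.** The week-9 change in VAS is compared by a two-sided Student's t-test, and MCLCS is handled similarly. For the course through day 7, the VAS and MCLCS changes "from baseline to day 7 to 9 weeks and will be explored graphically between the arms".

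**The concern.** The label on the objective and the timing of the measurement do not match. A patient seen exactly on schedule is on the first day at 300 mg, and a patient seen early in the window has not reached it. For MCLCS the recall week pulls the measurement further back, into lower doses and, at early visits, into days before treatment.

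What is at stake is interpretation. A small or absent difference at day 7 could be reported under a heading that names 300 mg, although the exposure behind it is mostly the escalation doses. One day-7 variable also pools patients at different points of the escalation. Finally, the objective is a comparison with placebo, while the method the protocol names for it yields no estimate and no interval.

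**Working it through.** **The plan's own figures.** The protocol gives no power or precision for day 7. Its only calculation is for week 9: noncentrality 0.5 × √(64/2) = 2.828, and the noncentral t with 126 degrees of freedom gives power 0.8015, as stated. That figure is not in question here.

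**Inputs.** Daily doses from the Section 3.5 table: 75, 75, 150, 150, 225, 225 mg on treatment days 1-6, and 300 mg from day 7. Window of three days either side of day 7, from Section 3.6. Recall of one week for MCLCS, from the Introduction.

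**Dose before and at the visit.** Mean of days 1-6 = (75+75+150+150+225+225)/6 = 900/6 = 150 mg. The protocol does not define day numbering, so both readings are shown.

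- If the day of randomisation is day 1, the window is treatment days 4-10. The scheduled dose at the visit is 150 mg on day 4, 225 mg on days 5-6 and 300 mg on days 7-10. Completed days at 300 mg before the visit: none for days 4-7, then 1, 2 and 3 for days 8, 9 and 10.
- If day 7 means seven days elapsed, the window is treatment days 5-11. The scheduled dose is 225 mg on days 5-6 and 300 mg from day 7. The on-schedule visit (treatment day 8) follows one completed day at 300 mg, and the latest (day 11) follows four.

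**MCLCS recall week.** Mean daily dose = sum of doses over the seven recall days / 7, with untreated days counted as zero. The number of untreated days is in brackets.

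| Counting | Earliest visit | On-schedule visit | Latest visit |
| --- | --- | --- | --- |
| Randomisation = day 1; visit day not in recall | day 4: 300/7 = 43 mg (4) | day 7: 900/7 = 129 mg (1) | day 10: 1650/7 = 236 mg (0) |
| Randomisation = day 1; visit day in recall | day 4: 450/7 = 64 mg (3) | day 7: 1200/7 = 171 mg (0) | day 10: 1800/7 = 257 mg (0) |
| Seven days elapsed; visit day not in recall | treatment day 5: 450/7 = 64 mg (3) | day 8: 1200/7 = 171 mg (0) | day 11: 1800/7 = 257 mg (0) |
| Seven days elapsed; visit day in recall | treatment day 5: 675/7 = 96 mg (2) | day 8: 1425/7 = 204 mg (0) | day 11: 1950/7 = 279 mg (0) |

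**First full recall week at 300 mg.** This is days 7-13, so it needs a visit on treatment day 13 (visit day counted) or day 14 (not counted). The latest visit allowed is treatment day 10 or 11. No in-window visit qualifies under any counting.

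**Effect on the MCLCS contrast.** The protocol gives no dose-response figure and no expected spread of visit days, so the loss over the whole trial cannot be computed. As an illustration, assume the full effect starts with the first dose and patients weight the seven recall days equally. With 4, 3 or 2 untreated days the earliest visit then keeps 3/7 = 43%, 4/7 = 57% or 5/7 = 71% of the contrast. If the effect grows with dose, less is kept.

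**The case against.** The dose phrase can fairly be read as a label for the regimen. The same parenthesis is attached to the primary objective and to most of the secondary ones, and Section 3.4 defines the active arm as starting at 75 mg with escalation. On that reading objective 2 asks about early response under the assigned regimen, which a blinded randomised comparison at about one week can answer. This stands.

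Three stronger readings are tempting, and the documents do not support them.

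- A reader might infer that the objective cannot be answered or that the comparison is biased. Both arms share the escalation scheme, the visit window and the blinding, so the timing affects what is measured and how sensitively. It does not favour either arm.
- A reader might infer that nothing at this visit reflects 300 mg. Visits in the later part of the window take place while 300 mg is scheduled and after up to three or four completed days on it. The recall argument concerns MCLCS only, since no recall period is stated for the VAS.
- A reader might infer that no day-7 analysis exists. The statistical analysis plan is not at hand and could add one, and a descriptive graph of a secondary time point is a legitimate choice.

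What remains is that the protocol itself names a comparative objective and assigns it a method that gives no estimate. The exact milligram figures also depend on day counting, which is why the table gives all four combinations.

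**Conclusion.** The point holds as a minor one. Day 7 measures early response during or just after dose escalation, under a heading that names 300 mg. An on-schedule visit has 0 or 1 completed days at 300 mg behind it. The earliest visits fall at 150 or 225 mg, and their MCLCS recall week has 3 to 4 untreated days (2 if elapsed days are counted and the visit day is included). No in-window visit has a full recall week at 300 mg. Early visits are therefore likely to reduce the MCLCS contrast, by an amount the protocol does not allow one to quantify.

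This rests on the Section 3.5 table. If the 7-day escalation in Section 3.4 were taken literally, 300 mg would begin a day later and the mismatch would be slightly larger. The week-9 primary analysis and the sample size are unaffected.

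**What to change.** 1. Reword objective 2, in the synopsis and in the objectives section, as early response to the assigned regimen during or just after escalation, without the 300 mg label at this time point.
2. Define day numbering (whether the day of randomisation is day 0 or day 1), and reconcile the escalation length in Section 3.4 (7 days) with the Section 3.5 table (6 days).
3. Make the visit window one-sided, day 7 to day 10, so that no assessment falls before escalation ends. By the table, untreated days in the MCLCS recall week then fall from as many as 4 to at most 1. If the reconciled escalation ends later than the table shows, the opening day of the window moves with it.
4. Report the day-7 between-arm difference in change for VAS and MCLCS with 95% CI, by the method Section 5.2 uses for the week-9 change (or adjusted for baseline), labelled as secondary. The graph can stay alongside it.

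The cost is a few sentences of wording, two estimates per report and slightly less visit flexibility. No dose changes. The fix reduces the mismatch but does not give a full MCLCS recall week at 300 mg, and the trial report should say so.

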# Study Methodology

### **3.1 Study Population and setting:**

Patients with suspected/diagnosed lung cancer complaining of cough lasting 2 weeks or longer despite the use of standard cough therapy will be screened for the study. The study will be conducted in the department of medical oncology at Tata Memorial Center located in Mumbai, Maharashtra.

### **3.2 Inclusion criteria**

1. Age 18 years or older.
2. Locally advanced or metastatic suspected or diagnosed NSCLC.
3. Eastern Cooperative Group performance status between 0 and 2.
4. Moderate (grade 2) or severe (grade 3) cough that has lasted for 2 or more weeks. Cough severity will be according to the Common Terminology Criteria for Adverse Events (CTCAE), v.5, in which grade 2 signifies moderate symptoms, medical intervention required, limiting instrumental activities of daily living; and grade 3 cough signifies severe symptoms limiting self-care activities of daily living.
5. Willing and able to limit to one alcoholic beverage per day (e.g. 360 ml of beer or 120 ml of wine or 330 ml of cooler or 43 ml of hard liquor like whisky/vodka/rum/gin).
6. Creatinine clearance measured by the Cockcroft-Gault formula > 60 ml/min.
7. Women of childbearing potential must be willing to consent to using effective contraception (e.g., hormonal contraceptives, bilateral tubal ligation, barrier with spermicide, intrauterine device) while on treatment and for at least 3 months thereafter. A man who is the partner of a woman of childbearing potential must be willing to consent to using effective contraception (e.g., vasectomy or barrier with spermicide) while on treatment and for 3 months thereafter.
8. Capable of providing informed consent and follow trial procedures.

